### Definitions

3.7

•**Current cigarette smoker:** Average of ≥5 cigarettes daily use in at least the year before enrollment.•**Successful smoking cessation:** Continuous abstinence in at least 4 weeks during 6 months following up.•**Uncontrolled DLP:** Description for uncontrolled DLP will be based on the serum level of LDL-C which depends on the concomitant comorbidities including diabetes mellitus and CVD [18]. The related cut-off value for the serum level of target LDL-C is ≤ 55 mg/dL. Values more than the listed cut-off value are considered uncontrolled DLP.•**Controlled DLP**: Lowering serum level of LDL-C by < 55 mg/dL and ≥50% reduction from baseline in any of the follow-up visits at the end of 3 and 6 months from randomization and remaining controlled in the next visits during the study.•**Uncontrolled HTN:** A patient who has a history of HTN with/without using the antihypertensive drug is considered hypertensive. Participants will be considered as having uncontrolled HTN according to the ACC/AHA guidelines [19].•**Controlled HTN:** Maintaining BP below the target treatment level (130/80 mmHg) at the time of office measurements (average of 2 readings obtained on 2 separate occasions with proper patient preparation and appropriate technique) at the end of 3 and 6 months from randomization and/or during one-week daily home measurements (average of records) before clinic visits.

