### Participants

3.8

According to eligibility criteria (Table 1), 1544 individuals will be selected. Participants in both arms will receive their routine care and the intervention arm will be encouraged to follow guides for each risk factor using the app in addition to the routine care. After 3 and 6 months, the status of risk factors will be determined through outpatient visits and face-to-face interviews for both arms. All the participants will be visited in an outpatient clinic by a cardiologist to evaluate the status of the risk factors and document any cardiovascular events (outcomes). Any additional visits will be considered for any patient requiring fewer interval visits.

During study time, patients in the intervention arm will be encouraged to continue to use the app. The patients in both arms will be allowed to have their routine care inside and outside THC whenever needed. The participant timeline and summary of the study protocol are summarized in Table 2 and Fig. 1, respectively.

**Table 2 tbl2:** Participant timeline.

		Study period			
		Enrollment	Allocation	Post-allocation	Close-out
**Month**		−3 ± 2 days	0	3	6
**Enrollment**		×			
**Eligibility screen**		×			
**Informed consent**		×			
**Allocation**			×		
**Intervention**			×	×	×
**Assessment**	Baseline variables	×		×	×
	Measuring systolic and diastolic blood pressure	×		×	×
	Evaluating smoking status	×		×	×
	Measuring low-density lipoprotein cholesterol serum level	×		×	×
	Evaluating adherence to treatment and diet			×	×
	Evaluating the usability (data entry) and satisfaction level of software/application			×	×

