### Data collection and statistical analysis

3.11

We are going to record all the patient's demographic and clinical characteristics.

(Including past medical history, duration of each disease, drug and habitual history, etc.) and status of their risk factors (controlled/uncontrolled). BP, height, weight, and waist circumference will be measured during each visit. The blood sample will be taken before each visit to measure the serum level of the following factors: Creatinine, LDL-C, Glycated hemoglobin (HbA1C), Total cholesterol, High-density lipoprotein (HDL-C), Fasting blood glucose (FBS) and Triglyceride. In addition, we will request all the patients to present every laboratory test report that was done even outside THC and all other documents related to any event that required hospitalization within the last year. Hypertensive patients in the control arm will receive a paper-based chart to document their BP (systolic and diastolic) for 7 consecutive days in each month (the intervention group will also enter and save the measurements in the app).

The data will be collected from a paper questionnaire which is filled out by the research team and saved information on the digital server. Data entry will be conducted on the IBM SPSS software database.

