### Statistical methods

3.12

Continuous variables will be presented through mean with the standard deviation (SD) for normally distributed variables or median with the interquartile range boundaries for skewed variables. Categorical variables will be presented as the frequency with percentage. To check the normality distribution of continuous variables, histograms will be applied along with the above descriptive quantities. Risk factors’ status will be measured at different time points to determine the final status at the end of certain time points. We will compare the prevalence of the controlled risk factors in time points of 0 (baseline), 3 and 6 months between intervention and control groups using x^2^ tests at each point. Multivariate logistic regression analysis will be used to determine the effect of the intervention on the control of risk factors at the end of 6 months. The effect will be reported as Odds Ratios with the corresponding 95% confidence interval. This will be a per-protocol approach. To perform the intention-to-treat method, participants will be analyzed according to the group they were allocated not the actual intervention they received. The missing values for subjects who were lost to follow-up or did not cooperate until the end of the study will be evaluated to see to what extent the missing data are completely random. If missing data do not violate the randomness assumption, they will be replaced using the multivariate missing imputation method. Otherwise, stratified analysis and sensitivity analysis for missing data will be considered. Finally, the size of the effect is measured and reported as a relative risk/risk ratio with a corresponding 95% confidence interval. The effect will be calculated and reported as a hazard ratio with the corresponding confidence interval.

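### No baseline-adjusted intention-to-treat comparison is fixed for controlled hypertension or dyslipidemia, although baseline BP and LDL-C are collected in every patient; the power at stake is small

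*Protocol article*

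**What the plan says.** All references are to the protocol article.

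- **Test.** Section 3.12 (Statistical methods) states: "We will compare the prevalence of the controlled risk factors in time points of 0 (baseline), 3 and 6 months between intervention and control groups". The method is a chi-square test at every one of these visits.
- **Regression.** The same section adds: "Multivariate logistic regression analysis will be used to determine the effect of the intervention on the control of risk factors at the end of 6" (that is, at the month-6 visit), reported as odds ratios. No covariates are listed. The sentence after the odds-ratio statement reads "This will be a per-protocol approach". The intention-to-treat sentence that follows says how patients are grouped but names no model.
- **Data at hand.** Table 2 (section 3.8) marks "Measuring systolic and diastolic blood pressure" and "Measuring low-density lipoprotein cholesterol serum level" at enrolment, month 3 and month 6. Section 3.11 confirms this: "BP, height, weight, and waist circumference will be measured during each visit", with LDL-C among the blood tests taken before each visit.
- **Outcomes.** Section 3.7 defines controlled HTN through "Maintaining BP below the target treatment level (130/80 mmHg) at the time of office measurements" and/or the average of one week of home readings. Controlled DLP needs LDL-C under 55 mg/dL together with a fall of at least 50% from baseline.
- **Randomisation.** Section 3.10 stratifies by seven combinations of uncontrolled risk factors, in blocks of at most 10.

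**The concern.** Controlled HTN and controlled DLP are yes/no readings of follow-up BP and LDL-C, and the same measures are taken at enrolment. Baseline severity should predict who reaches target, most plainly for BP. The seven randomisation levels balance which factors are uncontrolled, not how far above target they are. A chi-square test leaves that variation, and any chance imbalance in severity, in the comparison.

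The month-0 test does not help. Patients enter because a factor is uncontrolled, and blocks of at most 10 hold the arms within about 5 patients of each other in each level. The test therefore checks what the design already forces, and nothing is adjusted on the strength of it.

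At stake is precision, not validity. It matters most for hypertension, where the expected number of patients leaves power well short of 80%.

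**Working it through.** **1. The plan's own sample sizes.** Table 3 gives control vs intervention rates and n per arm including 10% loss. With the pooled two-proportion formula

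n = [z(α)·√(2p̄q̄) + z(0.80)·√(p₁q₁ + p₂q₂)]² / (p₂ − p₁)²

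and α = 0.05 **one-sided**, HTN (0.11 vs 0.165) gives [1.645 × 0.4870 + 0.8416 × 0.4855]² / 0.055² ≈ 484, and 484/0.9 ≈ 538, as stated. DLP gives 231, then 257, as stated. Smoking gives 695, then 773, against 772 stated. Two-sided α gives 684, 327 and 980 and does not reproduce the table. At the stated sizes less 10%, two-sided power is therefore 70.1% for each factor; this is the unadjusted starting point below.

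**2. Completers per arm.**
- HTN at its Table 3 size: 538 × 0.9 ≈ 484.
- HTN expected, if Table 3's 47% applies to enrolled patients: 772 × 0.9 × 0.47 ≈ 326.
- DLP at its Table 3 size: 257 × 0.9 ≈ 231.
- DLP expected, at 72%: 772 × 0.9 × 0.72 ≈ 500.

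**3. Upper bound: simple cut-off, untruncated normal baseline.** A normal follow-up value with correlation ρ to baseline was cut to give the Table 3 rates. A two-sided chi-square test was compared with a likelihood-ratio test of arm in a logistic model with baseline (3,000 to 4,000 trials per setting, Monte Carlo standard error about 1 point). ρ is an assumption.

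| Setting | Chi-square | Adjusted, ρ = 0.3 | ρ = 0.5 | ρ = 0.7 |
|---|---|---|---|---|
| HTN, 484 per arm | about 70% | 72-73% | 76-77% | 83% |
| HTN, 326 per arm | about 53% | 54-55% | 58% | 66-67% |
| DLP, 231 per arm | about 70% | 72-73% | 75-77% | 85% |
| DLP, 500 per arm | about 95% | 96-97% | 98% | 99% |

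**4. HTN with entry above the cut-off.** The patients in this comparison enter uncontrolled, so the baseline distribution is cut off below. With a half-normal baseline and 484 per arm:
- ρ = 0.3: 71% to 72%.
- ρ = 0.5: 71% to 74%.
- ρ = 0.7: 70% to 77% (6 to 7 points after rounding).

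If the restriction to patients above the cut-off is also allowed to weaken the correlation, the gain falls to about 0-3 points at 484 per arm. In truncated runs at 326 per arm the gain was about 1 point at ρ = 0.3 and 0.5 (52% to 53%) and 5 points at 0.7 (51% to 56%), or 2-3 points over the whole range in a separate run.

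**5. DLP under the section 3.7 rule.** Success requires follow-up LDL-C below the smaller of 55 and half the baseline value:

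| Entry LDL-C (mg/dL) | Must reach | Fall needed |
|---|---|---|
| 60 | 30 | 50% |
| 110 | 55 | 50% |
| 150 | 55 | 1 − 55/150 = 63% |
| 200 | 55 | 1 − 55/200 = 72.5% |

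The required percentage fall is flat up to 110 and rises after that, so a linear term captures little. This rule was simulated with log-normal LDL-C truncated above 55 (assumed pre-truncation means 85, 95 and 120 mg/dL, coefficient of variation 35%), rates 20% vs 30%, 231 per arm and ρ 0.3-0.7. A linear log term added about 0-3 points and a spline about 2-5; a separate run gave 0-1 and 2-3. Adjusted power at ρ = 0.7 was 71-75%, not the 85% in step 3.

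**The case against.** The best defence is that a chi-square test in a randomised trial is valid, that a multivariable regression is already planned for month 6, and that a condensed article may leave its covariate list to a SAP that is not shown. All of that stands, and it rules out several stronger readings.

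- A reader might infer that month 6 rests on chi-square tests alone. It does not: the regression is planned, and its unnamed covariates could include baseline BP or LDL-C.
- A reader might infer that baseline is used only for a between-arm test. It is not: baseline LDL-C is part of the controlled-DLP definition.
- A reader might infer that a patient entering just above the LDL-C cut-off has an easy target. The 50% rule removes that advantage for entry values from 55 to 110 mg/dL.
- A reader might take the gains of about 13 to 15 points in step 3 at ρ = 0.7 as the loss. They need an untruncated baseline and, for DLP, a different success rule.

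The defence does not supply an adjusted comparison at month 3, where the chi-square test is the only method named. Nor does it attach any adjusted model to the intention-to-treat analysis, since the label after the regression is per-protocol. The chi-square tests are a stated choice rather than an omitted detail.

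**Conclusion.** The point holds as a modest matter of efficiency. Section 3.12 fixes unadjusted tests for two outcomes whose baseline values are collected in everyone, and it fixes no baseline-adjusted intention-to-treat comparison at month 3 or month 6.

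With ρ between 0.3 and 0.7 and entry above the cut-off, the power forgone is roughly 0-6 points for HTN and 0-5 points for DLP. It would be larger only if baseline were not truncated. At the expected DLP number of about 500 per arm, unadjusted power is already about 95%, so the benefit there is mainly precision. These sizes rest on assumed correlations and LDL-C distributions that the documents do not give.

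No gain is shown for smoking, which sets the sample size, or for the 0-3 primary count; controlled HTN and controlled DLP are listed as secondary outcomes. It would be wrong to infer that the planned tests are biased or that substantial power is lost. The month-0 test is uninformative but does not harm the later inference.

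**What to change.** In section 3.12:

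1. Make the between-arm analysis of controlled HTN and controlled DLP, at months 3 and 6, an intention-to-treat logistic model with arm plus baseline. For HTN, enter systolic and diastolic BP as continuous terms. For DLP, enter LDL-C as a spline, because the required percentage fall changes slope at 110 mg/dL.
2. Report risk ratios and risk differences standardised from the model, with 95% CIs, and keep the raw percentages as description.
3. Drop the month-0 chi-square test and describe baseline by arm without p-values.

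The cost is a few sentences and a few lines of analysis code, with no new data, visits or patients. One small downside is that the adjusted odds ratio is conditional on baseline, so the standardised risks must be reported beside it. Section 3.12 already intends to report a risk ratio.

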### Sample size calculation

3.9

Farkouh et al. [22] which studied pooled data obtained from large randomized trials display the success rate in controlling risk factors in CAD patients for secondary prevention through lifestyle modification and drug consumption.

To increase the success rate percentage of modifying the risk factors by at least 1.5 times, concerning significance level of α = 0.05, study power of 80% and 10% loss of samples, a sample size of 257, 538, and 772 were considered for DLP, HTN, and CS, respectively. The largest sample size of 772 which is related to CS was selected (772 × 2 = 1544). The calculation was performed by G-power software. The final results are reported in Table 3.

**Table 3 tbl3:** Success rates in controlling Dyslipidemia, Hypertension and smoking and calculated sample size.

Risk Factor	Success rate percentage in the control group	Success rate percentage in the intervention group	Sample size in each group counting 10% shedding of samples	The abundance of patients referred to the Tehran Heart Center
**Dyslipidemia**	0.2	0.3	257	0.72
**Hypertension**	0.11	0.165	538	0.47
**Cigarette smoking**	0.08	0.12	772	0.34

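### The only named treatment-effect model is labelled per-protocol, neither analysis set is named primary, and the hazard ratio has no stated outcome or model behind it

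*Protocol article*

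**What the plan says.** Section 3.12 of the Protocol article starts with chi-square comparisons of the arms at baseline, 3 and 6 months. It then names its one model for the treatment effect: "Multivariate logistic regression analysis will be used to determine the effect of the intervention on the control of risk factors". This model concerns status at month 6, and its measure is stated separately: "The effect will be reported as Odds Ratios with the corresponding 95% confidence interval". The next sentence gives the analysis set: "This will be a per-protocol approach".

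Intention-to-treat comes directly after, described as an analysis in which "participants will be analyzed according to the group they were allocated not the actual intervention they received". No model is attached to it and no rank is given. A passage on missing data and imputation follows, and then two further effect measures. The size of the effect is to be "reported as a relative risk/risk ratio with a corresponding 95% confidence interval", and the closing sentence reads: "The effect will be calculated and reported as a hazard ratio with the corresponding confidence interval".

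Four other sections bear on this:

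- Section 3.6 (Study outcomes) defines the primary outcome as four ordered categories, from no controlled risk factor to three, measured at 3 and 6 months. Control of single factors and of combinations is secondary.
- Section 3.9 (Sample size calculation) states the design target as a ratio of success rates: "To increase the success rate percentage of modifying the risk factors by at least 1.5 times".
- Section 3.10 stratifies randomisation into seven levels by type and number of risk factors.
- Section 3.5.2 measures app adherence by logins, pages viewed and questionnaires completed.

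**The concern.** A per-protocol estimate is not protected by randomisation, because patients leave the analysis for reasons that arise after allocation. That matters more than usual here. App use exists only in the intervention arm, and section 3.5.1 describes ideal use as several times a day, so a set defined by app use could lose many intervention patients and no controls. If those who stop using the app also control their risk factors less well, removing them raises the intervention arm's success rate even when the app does nothing.

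The text does not settle which result answers the trial's question. With two analysis sets, three effect measures and no order among them, that choice stays open until the data are seen. One of the three measures, the hazard ratio, also presupposes event times that the protocol does not define.

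**Working it through.** **1. The design target and the three scales.** Table 3 gives control and intervention success rates p1 and p2. Formulas: risk ratio = p2/p1; odds ratio = [p2/(1−p2)]/[p1/(1−p1)]; grouped-time hazard ratio = ln(1−p2)/ln(1−p1).

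| Factor | p1 | p2 | Risk ratio | Odds ratio | Grouped hazard ratio |
|---|---|---|---|---|---|
| Smoking | 0.08 | 0.12 | 1.50 | 1.57 | 1.53 |
| Hypertension | 0.11 | 0.165 | 1.50 | 1.60 | 1.55 |
| Dyslipidemia | 0.20 | 0.30 | 1.50 | 1.71 | 1.60 |

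The stated 1.5-fold target is reproduced as a risk ratio for all three factors. The other columns are the same effects on other scales. They differ numerically, but none is an error in itself.

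**2. One-sided exclusion under no true effect.** The protocol gives no figures for this, so all inputs are assumptions: success is 14% in adherent-type and 8% in non-adherent-type patients in both arms, the mix is the same in both arms, a fraction a of the app arm is excluded as non-adherent, and no controls are excluded.

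Rate in the retained app arm = 0.14. Rate in the full control arm = (1−a)×0.14 + a×0.08. Spurious risk ratio = 0.14 divided by that rate.

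| a | Control-arm rate | Spurious risk ratio |
|---|---|---|
| 10% | 0.134 | 1.04 |
| 20% | 0.128 | 1.09 |
| 30% | 0.122 | 1.15 |
| 40% | 0.116 | 1.21 |

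**3. A second set of assumptions.** Fix the true rate at Table 3's 8% for smoking in both arms. Exclude 10% to 30% of the app arm, whose success rate is r = 0.25 to 0.75 times the arm average. Retained rate = (0.08 − a×0.08r)/(1−a).

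- Smallest (a = 10%, r = 0.75): retained rate 0.0822, odds ratio 1.03.
- Middle (a = 20%, r = 0.5): (0.08 − 0.008)/0.8 = 0.090, odds ratio 1.14.
- Largest (a = 30%, r = 0.25): (0.08 − 0.006)/0.7 = 0.1057, odds ratio 1.36.

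The true value is 1.00 throughout. The design odds ratio for smoking is 1.57.

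**4. What could carry a hazard ratio.** Set against sections 3.6 to 3.8:

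- Hypertension and dyslipidemia control are judged at the 3- and 6-month assessments.
- Dyslipidemia control reached at month 3 must also persist at later visits, so a month-3 event would depend on month-6 data.
- Smoking cessation is a period of abstinence within follow-up, but no event date is defined and status is read at the visits.
- Remaining an active app user can be observed in one arm only, so it gives no between-arm hazard ratio.
- No event time, censoring rule or survival model appears for any outcome.

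**The case against.** The strongest reply is that intention-to-treat is already in the plan, one sentence after the per-protocol label, and that the section ranks nothing. One fair reading pairs the odds ratio with per-protocol, and the risk ratio, which is the scale of the design target, with intention-to-treat after imputation. A reader might infer that the trial's headline result will be the per-protocol odds ratio. The document does not say so, and that inference should not be drawn. What stands is that the one model named for the treatment effect carries the per-protocol label, while intention-to-treat has neither a model nor a rank.

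Second, the per-protocol set is never defined, so nothing says that non-users will be dropped or that all controls will be kept. This is correct, and it makes the bias argument conditional. A condensed article may leave the definition of that set to a fuller document. The attachment of the effect model to it, however, is stated here.

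Third, a reader might infer that a hazard ratio cannot be estimated from these data. That goes too far: a complementary log-log model for grouped times could produce one from the two visits, as the table under the working shows. The sentence might also be a misplaced plan for cardiovascular events, which section 3.8 says will be documented at visits. But those events are not listed as outcomes in section 3.6, and no such model is named.

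Fourth, preferring a risk ratio to an odds ratio is not a correction, since both test the same null. That is accepted: the difference in scale alone would not justify a change.

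**Conclusion.** The point holds in this form: section 3.12 ties its only named effect model to a per-protocol approach, fixes no primary analysis set and no main measure, and ends with a hazard ratio that no stated outcome, event time or model supports. Followed as written, the modelled 6-month effect is a non-randomised comparison.

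The size of any bias cannot be known from the document. Under the first set of assumptions the spurious risk ratio is about 1.04 to 1.21, against a design target of 1.5. Under the second, the spurious odds ratio for smoking is 1.03 to 1.36. Both rest on three assumptions: app use defines the per-protocol set, exclusions fall on the intervention arm alone, and non-users do worse than users. If exclusions were balanced between the arms, or non-users did no worse, the bias would shrink or disappear; if non-users did better, it would reverse.

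**What to change.** Amend section 3.12 as follows:

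- State that the primary 6-month analysis is intention-to-treat, with all randomised patients in their allocated arm. Attach the regression model to it and adjust for the seven randomisation strata.
- Make per-protocol a supportive analysis, with adherence defined before the data are examined.
- Name one main effect measure in advance for each outcome. The ordered four-category primary outcome in section 3.6 needs its own, for example a common odds ratio from a proportional-odds model. For the single-factor binary outcomes the risk ratio matches the 1.5-fold target in section 3.9, and the odds ratio can be supporting output.
- Delete the hazard-ratio sentence, or define the time-to-event outcome, event date, censoring rule and model it refers to.

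The cost is a few sentences and no new data. The drawback is that the intention-to-treat estimate may be smaller than the per-protocol one.

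### Imputation is tied to the missing data looking random, so the plan commits to it where it is least needed and not where loss depends on month-3 status

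*Protocol article*

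**What the plan says.** All of the relevant text is in Statistical methods (3.12) of the Protocol article, directly after the sentence that defines intention-to-treat: "participants will be analyzed according to the group they were allocated not the actual intervention they received". The rule has three steps.

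1. **What is examined.** It concerns "The missing values for subjects who were lost to follow-up or did not cooperate until the end of the study". These values are "evaluated to see to what extent the missing data are completely random".
2. **If the check is passed.** "If missing data do not violate the randomness assumption, they will be replaced using the multivariate missing imputation method".
3. **If it is not.** "Otherwise, stratified analysis and sensitivity analysis for missing data will be considered".

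No other section changes this rule. The only planning figure for loss is in Sample size calculation (3.9): "concerning significance level of α = 0.05, study power of 80% and 10% loss of samples". Participants (3.8) and Table 2 show that blood pressure, LDL-C and smoking status are recorded at baseline, 3 months and 6 months in both arms.

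**The concern.** The only kind of randomness the text names is complete randomness, so the natural reading is that imputation is used when data are missing completely at random (MCAR). That is the situation in which complete cases are already unbiased; imputation does no harm and may add precision, but it is not needed to remove bias. Imputation earns its place when loss depends on data already observed, such as whether a patient was controlled at month 3. A check for complete randomness should then fail, and the plan moves to its open-ended fallback.

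The randomness in step 2 might instead mean missing at random (MAR). MAR concerns the unseen values, and observed data cannot verify it, so the gate cannot do its job on that reading either. MCAR cannot be confirmed either, since failing to detect a departure does not prove there is none. On both readings the handling of missing outcomes is settled only after the data have been looked at.

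At stake is the 6-month comparison of control rates. Participants know whether they have the app or paper materials (only the evaluating practitioners are described as blinded in 3.10), so loss that works differently by arm is possible. The documents do not say that it will happen.

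**Working it through.** **The plan's own figures.** The plan gives no number for this rule. Its sample sizes per arm in Table 3 (257, 538, 772) reproduce as 257, 538 and 773 with a pooled two-proportion formula, one-sided α = 0.05, 80% power and division by 0.90. The sidedness is a separate matter. What is used here is the 10% loss, the smoking rates of 0.08 and 0.12, and 772 per arm.

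**Illustration with no true effect (one risk factor, controlled yes/no).** Assumed, not from the documents:
- 20% are controlled at month 3 in both arms.
- The probability of control at month 6 is 0.70 if controlled at month 3 and 0.075 if not.
- True month-6 rate: 0.2 × 0.70 + 0.8 × 0.075 = 0.14 + 0.06 = 0.20 in both arms.
- App-arm loss is unrelated to status, so its complete-case rate stays at 0.20.
- Control-arm loss is five times as frequent among those uncontrolled at month 3.

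With loss L1 if controlled and L0 if not, the complete-case rate is

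[0.2(1 − L1)(0.70) + 0.8(1 − L0)(0.075)] / [0.2(1 − L1) + 0.8(1 − L0)].

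*At the planned 10% loss.* 0.2 L1 + 0.8 × 5 L1 = 4.2 L1 = 0.10, so L1 = 0.0238 and L0 = 0.1190.
Rate = (0.2 × 0.9762 × 0.70 + 0.8 × 0.8810 × 0.075) / 0.90 = (0.1367 + 0.0529) / 0.90 = 0.2106.
Risk ratio, app to control = 0.20 / 0.2106 = **0.95**.

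*At 21% loss* (L1 = 0.05, L0 = 0.25; 0.01 + 0.20 = 0.21).
Rate = (0.133 + 0.045) / 0.79 = 0.2253.
Risk ratio = 0.20 / 0.2253 = **0.89**.

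Swapping the arms reverses the direction: 0.2106 / 0.20 = 1.05 and 0.2253 / 0.20 = 1.13.

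Imputation within arm and month-3 status recovers the truth: the observed rates within status are still 0.70 and 0.075, and weighting them by the full 0.2 and 0.8 returns 0.20.

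**Check with the plan's smoking rates.** True rates are 0.08 and 0.12 (difference 0.040, risk ratio 1.50). Assumed: month-3 rate equal to month-6 rate; 80% of those controlled at month 3 stay controlled; control-arm loss 10% at random; app-arm loss 2% if controlled at month 3 and higher otherwise.

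- App-arm loss 10%: L0 = (0.10 − 0.12 × 0.02) / 0.88 = 0.111. Month-6 control if uncontrolled at month 3 = 0.024 / 0.88 = 0.0273. Complete-case rate = (0.12 × 0.98 × 0.8 + 0.88 × 0.889 × 0.0273) / 0.90 = 0.1282. Difference 0.048, risk ratio 1.60.
- App-arm loss 20%: rate 0.1409, difference 0.061, risk ratio 1.76.
- Same mechanism in both arms, 10% loss: 0.0856 and 0.1282. Difference 0.043, risk ratio 1.50.
- Completely random loss: difference 0.040, unbiased.

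Simulation of the arm-dependent pattern with both true rates at 0.08 (772 per arm, 2000 runs, two-sided 0.05) rejected in 6.2% of runs on complete cases at 10% app-arm loss and 14.7% at 20%. With multiple imputation within arm and month-3 status (10 imputations) it rejected in 5.6% and 4.9%. The simulation standard error near 5% is √(0.05 × 0.95 / 2000), about 0.5 percentage points, so the excess at 10% loss is slight.

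**The case against.** The strongest defence is that step 2 omits the word for complete randomness. If MAR was meant, imputing under MAR and turning to sensitivity analyses otherwise is a conventional order. That is a fair alternative reading, but it does not rescue a gate whose condition cannot be checked, and the preceding sentence names complete randomness alone. The text also names no formal test, so the check may be informal; the choice would still follow the data.

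Several stronger conclusions are tempting, and the documents do not support them.

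- *That imputation is abandoned when the check fails.* This is an inference from the contrast between the two sentences. The text does not forbid imputation and does not say the main result will rest on complete cases. It simply commits to nothing definite.
- *That any dependence of loss on observed data biases the result.* Loss that depends on arm alone leaves the proportions within each arm unbiased. Loss that depends on arm and randomisation stratum can be handled by a stratified analysis, the plan's own fallback. With the same mechanism in both arms at 10% loss, the risk ratio stayed at 1.50.
- *That intention-to-treat is given up.* The plan commits to analysis by allocated group, and a vague fallback does not undo that.
- *That the bias is large.* The larger figures need about twice the planned loss.

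A stratified analysis on the right predictors of loss could also remove the bias, but none is named. Month-3 status, the predictor that matters most here, is measured after randomisation, so comparing arms within its levels would condition on something the app may have changed.

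Imputation-model details are commonly left to a fuller document, and their absence is no fault. The point concerns the decision rule that the article does state.

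**Conclusion.** The rule is wrong as written and should be changed. It commits to imputation where complete cases are already unbiased, and to nothing definite where loss depends on observed post-baseline status. The 6-month comparison can then be biased if that dependence differs by arm. Reading the condition as MAR does not repair it.

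The size is modest at the planned 10% loss: a risk ratio of about 0.95 with no true effect, or 1.60 in place of 1.50 under the smoking assumptions. It grows with loss, to 0.89 at 21% and to 1.76 at 20% app-arm loss. The direction can go either way. The loss patterns and the month-3 to month-6 transition rates are assumptions; the documents give only the total loss and the target rates. The illustrations also assume that patients lost by month 6 were seen at month 3. Those lost earlier could be imputed only from arm, stratum and baseline data.

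**What to change.** In Statistical methods (3.12):

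- Remove the condition on randomness. A description of the missing-data pattern can stay, but should not decide the method.
- State that the intention-to-treat analysis uses multiple imputation under MAR for all randomised patients, whatever any MCAR check shows, with arm, randomisation stratum, and baseline and month-3 risk-factor status in the imputation model.
- Commit to at least one missing-not-at-random sensitivity analysis, for example counting missing as not controlled, or a delta adjustment by arm.

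The cost is one rewritten paragraph and a little more analysis work. Table 2 already schedules the blood pressure, smoking and LDL-C assessments the model needs, and the stratum is known at randomisation, so no new data collection is required.
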